### Setting

The study will take place in Hong Kong, a city in southern China. The Hong Kong AIDS Council estimated 200,000 FSWs involved in the sex industry in Hong Kong [42]. Two local non-governmental organisations (NGOs), Action for REACH OUT and JJJ Association with long-term relationship with FSWs in Hong Kong will help recruit participants and the intervention will be conducted in their service centres. AFRO was founded in 1993 and has provided extensive outreach and personal connection network with the local and migrant FSWs. AFRO’s primary target groups are mainly street sex workers, nightclub and karaoke bar girls as well as one-woman brothel workers whereas JJJ Association was set up in 2008 by a group of FSWs working in one-woman apartments, sauna and massage parlours. They provide outreach visits, assistance for family and legal problems, as well as social activities for FSWs. One of the co-investigators (WW) has worked with these organisations for many years and the long-existing collaboration will allow the present study to recruit FSWs spread across many institutions and districts in Hong Kong.

### Participants

FSWs who fulfil the inclusion criteria will be invited and have the study explained to them by the trained outreach staff of the NGOs. Inclusion criteria for the proposed study are: (i) 18 years or older; (ii) acknowledged to have been living and working as a FSW in Hong Kong within the preceding 6 months; and (iii) able to give an informed consent. All potential participants will be screened over the telephone by one of the researchers who is a clinical psychologist to confirm their fulfilment of inclusion criteria and exclude them if they are (i) unable to speak Cantonese/ Putonghua; and (ii) diagnosed with and currently on medical or psychological treatment for a serious psychological health problems such as psychosis, current substance abuse, bipolar disorder, severe affective disorders or have suicidal ideation.

Eligible participants will be provided with further details of the study and those who provide verbal consent will complete the self-reported baseline questionnaire face-to-face. Participants will be randomly allocated on a 1:1 ratio into one of the two groups according to a block randomisation list which was computer-generated. Participants are informed that they would have an equal chance of allocating into any of the two groups and the allocation outcome is unknown to participants until baseline assessment session. The women recruited will be advised not to disclose the content and activities of the intervention to others to avoid contamination. An independent researcher will conduct the baseline, post-intervention, and follow-up assessments and enter the data obtained from the questionnaires.

### Sample size

Sample size estimation is based on the “always” use condom rate during commercial transactions in the last month at 49.3% from the latest local study published on the topic [16] and an assumption of effect size of 25% on condom use rate between the intervention and control groups from a previous study [43]. In order to detect such a difference with a power of 80% and a two-tailed significance of 0.05, the sample size required is 66 in each group.

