**Methods:**

A total of 132 FSWs will be recruited and randomly assigned to either the intervention or usual care (control) groups in a multi-centred randomised controlled trial. Based on the resilience framework, this intervention is comprised of six weekly sessions focused on the awareness, expression and management of emotions, identifying roles and personal strengths, and effective problem-solving skills. Complex intervention assessment on both intervention process and effectiveness will be adopted when the primary outcome reduction of sexual risk behaviour and other psychological outcomes include their perceived stress, self-esteem, self-efficacy, coping overall resilience, and psychological distress will be measured at baseline, post-treatment and 3-month post-intervention and differences assessed by ANOVA. The relationship of resilience factors, psychological health and HIV preventive behaviours will be evaluated using structural equation modelling.

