The programme will be conducted by the first author, who is a clinical psychologist supervised by the investigators based on a programme manual with objectives, outlines, activities and hand-outs. While participants must attend the first and the last sessions in order, they are able to attend the other four “stand alone” session in an order according to their schedule. Based on our previous work with FSWs, special arrangements are proposed to address the practical and psychological needs to increase participation rates: (1) FSWs will be initially contacted and subsequently followed up by the outreach staff of the NGOs, whom they have established long-term contact and trust; (2) stand-alone sessions and a more flexible time intervals are unique from usual cognitive behavioural therapy schedule in order to accommodate the mobile and erratic job nature of FSWs; (3) a relatively small group size of 3–6 persons will allow the participants to share their emotions and experiences in application of the newly acquired skills.

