### Limitations

Participants who volunteer for the study are arguably biased towards being more motivated and health-conscious but the design of randomised control trial equalises this effect in both groups. Furthermore there is the potential for the participants to have psychological distress and therefore screening by a clinical psychologist will help exclude those who are clinically depressed and need intensive treatment. Although the outreach staff will contact the FSW recruited regularly, the attrition rate of those who are motivated but assigned to the usual care group may be diminished and hence a potential tendency to drop out from the study. The aims and objectives of the study will be clearly explained to the potential participants and the “buy-in” will be sought before they agree to participate. Given Hong Kong is effectively one large metropolis and there are considerable overlaps between the two targeted NGOs, therefore, cluster randomised control trial will not be feasible. Even though the participants recruited from the two NGOs would be told specifically not to disclose, there may still be a risk of contamination between the intervention and control group given the participants may know each other.

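### The 132 women recruited equal the number the protocol calls required, with no stated attrition allowance; 80% power survives little or no loss, and the planned ANOVA of change may miss it with none

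*Protocol article*

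**What the plan says.** The Sample size section takes the control rate from a local study, the always "use condom rate during commercial transactions in the last month at 49.3" per cent, and adds "an assumption of effect size of 25% on condom use rate between the intervention and control groups". It concludes, for each arm: "In order to detect such a difference with a power of 80% and a two-tailed significance of 0.05, the sample size required is 66". It names no formula, no continuity correction and no attrition allowance, and does not say whether the 25% is absolute or relative.

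The Abstract (Methods) says "A total of 132 FSWs will be recruited and randomly assigned", and 132 = 2 × 66.

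Loss to follow-up comes up elsewhere. The Limitations discuss motivated women "assigned to the usual care group may be diminished and hence a potential tendency to drop out from the study". The Usual care section requires controls who join another psychological programme to leave the trial. Under Study design, controls are assessed 6 to 12 weeks after baseline and again 3 months later.

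The Data analyses section plans analysis of variance, by intention to treat, of change over time between groups, for sexual health risks as well as for the psychological scales.

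**The concern.** The section presents 66 as the number the test needs for 80% power, and the same number is recruited. Taken at face value, every woman must supply an outcome, yet the protocol itself foresees that some may not. Unlike the handling of missing data, the recruitment target and its stated power are fixed in this document.

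The calculation compares two proportions at one time, whereas the planned analysis is an ANOVA of change, so the 80% does not describe the planned test even with full follow-up.

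What is at stake is how a null result is read. If true power is nearer 60% or 70%, a non-significant result says much less about a 25-point effect than the stated 80% suggests.

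**Working it through.** **Inputs from the protocol.** Control rate 0.493; difference 0.25, so 0.743 in the intervention arm; two-sided alpha 0.05; power 80%; 1:1 allocation; 66 per arm.

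**Assumed, because the protocol gives neither.** Loss of 5% to 30%, and a within-woman correlation r of 0.2 to 0.5 between baseline and follow-up condom use.

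**1. Reproducing 66.** The mean proportion is (0.493 + 0.743)/2 = 0.618. The null variance term is 2 × 0.618 × 0.382 = 0.4722. The alternative term is 0.493 × 0.507 + 0.743 × 0.257 = 0.2500 + 0.1910 = 0.4409.

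- Uncorrected: n = (1.960 × √0.4722 + 0.8416 × √0.4409)² / 0.25² = 58.1, so 59.
- Continuity-corrected: (58.1/4) × [1 + √(1 + 4/(58.1 × 0.25))]² = 65.86, so **66**.
- Uncorrected with 10% inflation: 59/0.90 = 65.6, so **66** again.
- Relative 25% (0.493 × 1.25 = 0.616): 255 uncorrected, 271 corrected. This cannot be what was meant.

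**2. Power after loss.** With m analysed per arm, uncorrected power is Φ[(0.25 − 1.960√(0.4722/m)) / √(0.4409/m)]. The corrected version replaces 0.25 by 0.25 − 1/m. At 20% loss, m = 52.8:

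- Uncorrected: (0.25 − 0.1853)/0.0914 = 0.71, giving 76.0%.
- Corrected: (0.25 − 0.0189 − 0.1853)/0.0914 = 0.50, giving 69.2%.

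| Loss | m per arm | Corrected | Uncorrected |
|---|---|---|---|
| 0% | 66 | 80.1% | 84.9% |
| 5% | 62.7 | 77.7% | 83.0% |
| 10% | 59.4 | 75.1% | 80.9% |
| 15% | 56.1 | 72.3% | 78.6% |
| 20% | 52.8 | 69.2% | 76.0% |
| 30% | 46.2 | 62.2% | 70.2% |

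Exact enumeration at 66 per arm agrees: Fisher 80.9%, Yates 80.2%, uncorrected chi-square 85.2%. The uncorrected test reaches 80% at about 12% loss (m = 58.1). The corrected one has no slack.

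**3. Power of the planned ANOVA of change.** I approximate it by comparing mean change (follow-up minus baseline, each 0 or 1), with both arms at 0.493 at baseline. The variance of change is 2 × 0.2500 × (1 − r) in controls and 0.4409 − 2r√(0.2500 × 0.1910) in the intervention arm. At r = 0.2 these are 0.400 and 0.354. The standard error at 66 per arm is √(0.754/66) = 0.107, and power is Φ(0.25/0.107 − 1.96), about 65%. Simulation gives:

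| r | 66 per arm | 53 per arm |
|---|---|---|
| 0.2 | 64% | 55% |
| 0.3 | 70% | 61% |
| 0.5 | 84% | 75% |

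**4. Baseline-adjusted analysis of the follow-up outcome.** Adjustment multiplies the variance by about (1 − r²), instead of adding the baseline variance as a change score does. At 53 per arm, the standard error is √(0.4409 × 0.96/53) = 0.0894 at r = 0.2 and √(0.4409 × 0.75/53) = 0.0790 at r = 0.5. Normal-approximation power is about 80% and 89%. Simulation gives slightly less, about 79% to 87%.

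**The case against.** The strongest reply is that 66 may already contain an allowance. An uncorrected 59 inflated for 10% loss is 66, and no document mentions a continuity correction. On that basis 66 per arm has about 85% power when all are analysed and stays at 80% up to about 12% loss. This stands. A reader might infer from the exact match with the corrected formula that dropout was ignored, or that follow-up must be complete; the protocol supports neither. It remains true that the section calls 66 the size required and mentions no inflation. If an allowance was intended, the sentence misdescribes its own figure.

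A second reply is that the shortfall depends on a rate the protocol does not give. That also stands: with full follow-up, the two-proportion comparison meets its 80%.

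Third, the evidence for loss should not be stretched. The phrase "in order to accommodate the mobile and erratic job nature of FSWs" in the Intervention procedure explains flexible session scheduling, one of several measures to raise participation; it does not forecast attrition. Outreach follow-up and seeking commitment before consent are further mitigation. The Limitations describe a potential tendency to drop out, not an expected rate.

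Finally, the ANOVA figures rest on an assumed correlation and a two-time-point simplification of a three-assessment design. At r = 0.5 with full follow-up, the change score does reach 84%. The claim is limited to the lower correlations.

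**Conclusion.** The point holds as one of under-specification with a measurable consequence. The figure of 66 reproduces, so it is not an arithmetic error. The protocol does not say how 66 was obtained, recruits exactly that number, and states no allowance for a loss it mentions itself. Whether 80% survives depends on the unstated route: up to about 12% loss with an uncorrected test, and none with a corrected one. At an assumed 20% loss, power is 69% to 76%, below target either way.

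Separately, the planned ANOVA of change falls short of 80% at correlations of 0.2 to 0.3 even with complete data (64% to 70%), under the two-time-point approximation.

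A reader might go further and conclude that the design cannot deliver 80% power. The documents do not support that: they give no dropout rate and no within-woman correlation, and a baseline-adjusted analysis comes close to 80% or exceeds it at 53 per arm. The matter should be corrected, but it does not undermine the trial.

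**What to change.** In the Sample size section:

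- Name the formula, and say whether 66 is the continuity-corrected number or 59 inflated for 10% loss.
- Write the effect as 25 percentage points (49.3% versus 74.3%).
- State the expected follow-up and the power at that follow-up. For example, 132 randomised with about 53 per arm analysed (66 × 0.80) gives about 69% to 76% power unadjusted.

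In the Data analyses section, replace the ANOVA of change for the primary outcome with a comparison of the binary outcome at follow-up, adjusted for baseline condom use. This uses data already collected and gives about 79% to 87% power at 53 per arm under the assumed correlations.

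The cost is a slightly less favourable stated power figure and an edit to two sections. No extra enrolment is needed.

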### Intervention procedure

Participants in the intervention group will receive 6 one-hour group sessions at one-to-three week intervals. There will be 3 to 6 participants in each group. These sessions target at the three major psychological resilient factors of self-esteem, self-efficacy (e.g. praise and self-rewards will be used) and coping flexibility based on resilience framework. The programme will be conducted in a group setting so that role-plays and group modelling and interactions will be used. Such an approach, informed by Social Cognitive Theory [34], espouses that individuals can learn from the actions of another person and from the regular reinforcement a person receives. Activities in these sessions will incorporate examples of their experience in daily life and at work aimed at promoting their awareness and expression of their emotions and thoughts, management of their emotions. Since the current intervention aims to promote psychological well-being, it also draws on the approach used by previous resilience interventions, including recognising and sharing positive thoughts and emotions, identifying personal strengths and ability, introducing a variety of coping strategies, and planning using their skills and strengths to achieve goals in the future. The outline of each session is listed in Table 1.

**Table 1 T1:** Programme Outline of PREP

**Session**	**Contents**
1. Starting out	Goal-setting, encouraging awareness and expression of emotions in reaction to events
2. Empowering interpretation	Emotion management, identifying negative thoughts and generating helpful thoughts
3. Effective problem-solving	Exploring effective coping strategies, practicing problem-solving with case scenarios
4. Who am I?	Recognising their roles, giving each other affirmation
5. The unique self	Identifying successful experiences and their strengths, expressing gratitude to others
6. Preparing for the future	Exploring obstacles and using their resources to deal future challenges

The programme will be conducted by the first author, who is a clinical psychologist supervised by the investigators based on a programme manual with objectives, outlines, activities and hand-outs. While participants must attend the first and the last sessions in order, they are able to attend the other four “stand alone” session in an order according to their schedule. Based on our previous work with FSWs, special arrangements are proposed to address the practical and psychological needs to increase participation rates: (1) FSWs will be initially contacted and subsequently followed up by the outreach staff of the NGOs, whom they have established long-term contact and trust; (2) stand-alone sessions and a more flexible time intervals are unique from usual cognitive behavioural therapy schedule in order to accommodate the mobile and erratic job nature of FSWs; (3) a relatively small group size of 3–6 persons will allow the participants to share their emotions and experiences in application of the newly acquired skills.

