### Data analyses

First of all, the baseline demographics of the intervention and control groups will be compared with independent sample *t*-tests for continuous variables and *chi*-square for categorical variables to assess the compatibility of the two-trial arms at baseline to ensure both groups were similar to start with. The change of scores on sexual health risks and psychological outcome measures (self-esteem, self-efficacy, coping, resilience and GHQ) over time between two groups will be analysed using analysis of variance with intention-to-treat analysis. Bivariate correlation analyses will be performed to examine the relationship between psychological variables and behavioural outcomes. Linear regressions will also be used to examine the associations and the effects of resilience, self-esteem, self-efficacy, coping on psychological health outcomes and HIV preventive behaviours. The statistical analyses will use SPSS 20.0 and *p*-values of 0.05 or less will be considered statistically significant.

The second objective of the current study is to explore the mechanism of how individual resilience factors influence the psychological outcomes and HIV preventive behaviours in FSWs (as proposed in Figure 1). Structural equation modelling (SEM) identifies connection strengths that best predict the observed structure of the data with respect to the specified model. Thus, SEM will be performed to evaluate the model fit of the proposed model that links psychological resources with harm-reduction behaviours as measured by condom use.

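### PREP is given in interacting groups of 3 to 6 in one arm only, but neither the sample size nor the stated ANOVA allows for correlation within those groups

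*Protocol article*

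**What the plan says.** Under Participants, women are allocated individually, 1:1. Under Intervention procedure, the intervention arm is then treated in small groups: "There will be 3 to 6 participants in each group". The group format is deliberate, chosen so that "role-plays and group modelling and interactions will be used". The same section lets the four middle sessions be taken in whatever order suits each woman; only the first and last are fixed. Under Usual care, controls have outreach visits, screening and optional social activities, and no assigned therapy group.

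The Sample size section takes a control rate given as "use condom rate during commercial transactions in the last month at 49.3" per cent and "an assumption of effect size of 25% on condom use rate between the intervention and control groups", "with a power of 80% and a two-tailed significance of 0.05", and concludes that "the sample size required is 66 in each group". The abstract gives the total: "A total of 132 FSWs will be recruited and randomly assigned". No ICC or design effect appears.

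Under Data analyses, the changes in sexual risk and psychological measures "over time between two groups will be analysed using analysis of variance with intention-to-treat analysis". PREP group is not mentioned. The Limitations section raises clusters only to say that cluster randomisation is not feasible and that the arms may contaminate each other.

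**The concern.** This is a partially nested design: individual randomisation, with grouped treatment in one arm. The plan relies on women in a PREP group learning from and affirming one another, so it is plausible that their outcomes will resemble each other more than those of women in different PREP groups. If so, 66 treated women carry less information than 66 independent women. A two-arm comparison without a group term then understates the variance of the intervention-arm mean. Intervals come out too narrow, p-values can be too small, and the stated power is somewhat optimistic.

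**Working it through.** **Inputs from the protocol.** Control rate 49.3%; effect 25%, read as 25 percentage points, giving 74.3%; two-sided alpha 0.05; power 80%; 66 per arm; group size m = 3 to 6 in the intervention arm only. Sixty-six women make 66/6 = 11 to 66/3 = 22 groups.

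**Assumption, not in the protocol.** ICC of 0.02 to 0.10.

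**Step 1: reproduce the 66.** The mean rate is (0.493 + 0.743)/2 = 0.618.

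n = [1.96 √(2 × 0.618 × 0.382) + 0.8416 √(0.493 × 0.507 + 0.743 × 0.257)]² / 0.25² = 58.1, so 59 per arm.

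With continuity correction: (58.1/4) × [1 + √(1 + 4/(58.1 × 0.25))]² = 65.9, so 66 per arm, an exact match. A relative 25% increase would need 255 per arm (271 with correction), so the absolute reading is the one used. The protocol does not name the formula. Since 59/0.90 also rounds up to 66, an unstated 10% dropout allowance would give the same figure. Neither route contains a clustering allowance.

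**Step 2: effect on the standard error and type I error.** The design effect in the intervention arm is DE = 1 + (m − 1) × ICC. With equal arms and equal variances, true SE / naive SE = √((1 + DE)/2). The type I error of the naive test is 2 × [1 − Φ(1.96 / ratio)].

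Example, m = 4.5 and ICC 0.10: DE = 1 + 3.5 × 0.10 = 1.35; ratio = √(2.35/2) = 1.084; type I error = 2 × [1 − Φ(1.808)] = 7.1%. The naive SE is 1 − 1/1.084 = 7.7% too small.

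**Step 3: power at 66 per arm for a test that allows for clustering.**

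Power = Φ[(0.25 − c − 1.96 s0)/s1], with s0 = √(0.618 × 0.382 × (1 + DE)/66), s1 = √((0.493 × 0.507 + 0.743 × 0.257 × DE)/66), and c = 1/66 with continuity correction or 0 without.

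Same example: s0 = 0.0917 and s1 = 0.0877, giving Φ(0.629) = 73.5% with correction and Φ(0.802) = 78.9% without.

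| m | ICC | DE | SE ratio | Type I error | Power, corrected | Power, uncorrected |
|---|---|---|---|---|---|---|
| any | 0 | 1.00 | 1.000 | 5.0% | 80.1% | 84.9% |
| 3 | 0.02 | 1.04 | 1.010 | 5.2% | 79.3% | 84.2% |
| 4.5 | 0.02 | 1.07 | 1.017 | 5.4% | 78.8% | 83.7% |
| 4.5 | 0.05 | 1.175 | 1.043 | 6.0% | 76.8% | 81.9% |
| 4.5 | 0.10 | 1.35 | 1.084 | 7.1% | 73.5% | 78.9% |
| 6 | 0.05 | 1.25 | 1.061 | 6.5% | 75.4% | 80.6% |
| 6 | 0.10 | 1.50 | 1.118 | 8.0% | 70.9% | 76.3% |

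The last row is the extreme of the range: every group at its maximum size and the ICC at its upper limit.

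**The case against.** - **Within-group correlation is not established.** A reader might infer that the outcomes will be correlated. The protocol makes that plausible but gives no ICC, and the primary outcome is each woman's own condom use with clients. One facilitator leads all groups, so variation between therapists, one usual source of correlation, is absent. The point must stay conditional.
- **The groups are not closed.** Four of the six sessions can be taken in flexible order, so membership may mix. The formula above assumes fixed groups and is therefore approximate. Mixing may dilute or spread correlation; it does not make the women independent.
- **Type I error does not rise in general.** A reader might infer that the nominal 5% test is anti-conservative whatever PREP does. If PREP changes nobody's outcome, individual randomisation protects the test even though groups are formed afterwards. Inflation needs group-specific effects that average to zero, or dropout or measurement that follows the groups.
- **Two stronger descriptions are unsupported.** One is that the ANOVA has a single error term: the text speaks of change over time, which suggests a repeated-measures form, and neither states nor excludes a nested term. The other is that controls are independent: they are visited by venue, may share activities run by the NGOs, and may know each other. Treating them as singletons is an approximation.
- **A fuller analysis plan might add a group term.** It might, and this weakens the analysis half of the point more than the sample-size half. The article nevertheless commits to an N with no clustering allowance and to a named comparison with no group term.
- **Power may have slack.** Without continuity correction, power stays at or above 80% for ICC up to 0.05 at every group size (80.6% at m = 6). With the correction, which reproduces the stated N exactly, there is none.

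**Conclusion.** The point stands in conditional form. If outcomes correlate within PREP groups, the plan as stated understates the standard error of the arm difference and overstates precision. At a mean group size of 4.5 and an assumed ICC of 0.02 to 0.10, the standard error is about 2% to 8% too small. Type I error is about 5.4% to 7.1%, under the conditions given above. Power at 66 per arm is about 79% to 74% rather than 80% with continuity correction, or about 84% to 79% rather than 85% without. Groups of 6 with ICC 0.10 give 8.0% and power of 71% or 76%; that is a limit, not an expectation.

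These figures rest on an assumed ICC, closed groups, independent controls and no dropout. A reader might conclude that the trial is invalid or must be enlarged. The documents support neither. This is a modest weakness that should be corrected in the analysis.

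**What to change.** - **Data collection.** Record the PREP group in which each woman starts, and which sessions she attends with whom. Attendance is already to be recorded under Process evaluation, so this adds only group composition.
- **Analysis.** Replace the two-arm ANOVA with a partially nested model that has a random effect for PREP group in the intervention arm only: logistic for the binary condom-use outcome, linear for the psychological scales. GEE with cluster-robust standard errors is an alternative. Either needs a small-sample correction, given about 11 to 22 groups.
- **Mixing.** State that starting group is an approximation to actual exposure. Add a multiple-membership sensitivity analysis if the attendance records show substantial mixing.
- **Reporting.** Report the estimated ICC, and restate power at 66 per arm as a range over assumed ICCs.

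No additional women need be enrolled, and delivery and visits are unchanged. The cost is revised analysis wording, slightly wider intervals and a slightly lower stated power.
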